## **9.2 Assessments of outcomes**

### **9.2.1 Assessment of primary outcome**

The primary end point will be the proportion of newly detected atrial fibrillation.

Recording will be done twice daily in the presence of specially trained nurses. In case of bad quality, the measurement will be repeated. The recordings will be validated through a web-based interface offered by Zenicor. The one-lead ECGs will be reviewed by the investigating physicians through the Web-based analysis service (Zenicor-ECG Doctor System) to assess the presence of AF.

The presence of an atrial fibrillation is defined as an irregularly irregular rhythm in the absence of discernable p waves or the presence of f-waves in at least one of the ECG registration.

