| Number of Participants with Rationale: | 
Based on previous research, we assume to detect AF in 1% of patients in the control group and in 3% of patients in the intervention group. The inclusion of n=745 patients per group would yield a power of 80% to detect that difference. In order to account for ineffective measurements, post-inclusion drop-outs or other unforeseen drop-outs, we seek to include n=800 patients per group.
                                                                                                                                                                                                                                                                                                                                                                                                                                                                                                                                                                                                                                                                                                                                                 |
| Study Duration:                        | 
Based on the current statistics pertaining to admissions and length of stay at our institution we estimate a total duration of 15 months for patient enrollment and the assessment of the primary end point. Clinical follow-up
                                                                                                                                                                                                                                                                                                                                                                                                                                                                                                                                                                                                                                                                                                                                                                                                                                                                                                                   |

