### **3.6 Risks / Benefits**

Guidelines strongly and uniformly recommend anticoagulation in patients with AF in order to reduce the thromboembolic risk. The benefits of oral anticoagulant therapy are directly proportional to the underlying stroke risk as measured by hypertension, age, diabetes mellitus, congestive heart failure, prior stroke, vascular disease, and gender (CHA2DS2 -VASc score). Despite the documented benefits of anticoagulation in high-risk patients, bleeding complications are a common concern with the use of anticoagulant. The factors associated with a higher bleeding risk are similar to those conferring a higher thromboembolic risk. Nevertheless, it is the patients with the highest thromboembolic risk that benefit the most from oral anticoagulant therapy.

A potential risk of the Detect-AF study is the overdiagnosis of atrial fibrillation. This might lead to a non-indicated anticoagulant treatment and might expose the patients to an unnecessarily increased bleeding risk.

However, every case of new AF diagnosed by use of the screening method will be reviewed by two independent cardiologists. In case of uncertainty, additional recordings, e.g. Holter or R-Test will be performed.

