#### **8.1.2 Control Intervention (standard/routine treatment / medical device)**

Patients allocated to the control group will not undergo systematic monitoring of AF. In those patients, recording of 12 lead ECG or any other monitoring modalities will be employed according to routine clinical practice.

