## **12.3 Monitoring**

The following assessment for a minimal risk study are completed:

- Study poses no more risk than expected in daily life (no risk in the skin-contact to the thumbs of the patient to the zenicor electrodes, routine blood draw, physical exam).
- No vulnerable population included
- Trial procedures is not clinically unusual and complex

A possible misinterpretation of Zenicor electrocardiograms could lead to diagnostic errors and to unadapted treatment. The zenicor method has shown a sensitivity of 96% and specificity of 92% in detection and diagnosis of atrial fibrillation when compared with 12-lead ECG. The somewhat lower specificity reflects that the device rather overdiagnose than neglect patients with atrial fibrillation.

However, each case of newly diagnosed atrial fibrillation by use of the Zenicor device will be examined by two independent cardiologists. In case of uncertainty, additional recordings (by Holter or R-Test) will be made. The risk of diagnostic errors is very close to the usual risk taken in routine practice.

An external monitoring of the study will be carried out retrospectively and prospectively:

- 1st on-site visit, intermediate visits and closing visit

- study risk analysis
- verification of source data
- CRF verification
- revision of consent forms
- verification of the recruitment procedure
- validation of eligibility criteria
- evaluation of the main evaluation criterion
- evaluation of Serious Adverse Reaction Assessment (SAE)

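### The primary endpoint can be met by one unblinded reading of one strip, and the planned two-cardiologist review is neither tied to it nor extended to the control arm

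*Protocol*

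**What the plan says.** Section 9.2.1 is the only operational description of how the primary outcome is assessed. It deals with Zenicor recordings: "The one-lead ECGs will be reviewed by the investigating physicians through the Web-based analysis service (Zenicor-ECG Doctor System) to assess the presence of AF". AF is present if the rhythm criterion is met on a single registration. Sections 8.1.1 and 12.2.3 also leave the reading to the investigators, and section 6.2.2 states that nothing is blinded. Section 9.2.1 names no second reader and no rule for a disputed reading. It does not say how AF found on a routine ECG, in either arm, enters the endpoint.

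A second look appears in two other places. Section 3.6 (Risks / Benefits) says "every case of new AF diagnosed by use of the screening method will be reviewed by two independent cardiologists", and section 12.3 (Monitoring) says "each case of newly diagnosed atrial fibrillation by use of the Zenicor device will be examined by two independent cardiologists", both with further recordings if there is doubt. Both are limited to cases found by screening. Neither says that a case the cardiologists reject leaves the primary outcome.

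In the control arm, "recording of 12 lead ECG or any other monitoring modalities will be employed according to routine clinical practice" (section 8.1.2). Section 9.3.3 offers everyone with newly detected AF a cardiology visit that includes a 12-lead ECG. This is clinical care, and no link to the endpoint is stated.

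On accuracy, section 12.3 states: "The zenicor method has shown a sensitivity of 96% and specificity of 92% in detection and diagnosis of atrial fibrillation". It adds that the device errs towards overdiagnosis, and section 3.6 names overdiagnosis as a risk of the study.

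**The concern.** The primary test compares two small proportions, so a handful of misclassified patients in one arm matters. Zenicor strips exist only in the screening arm, are taken at least twice daily, and one positive strip is enough. Reading errors therefore accumulate over a stay in that arm and have no counterpart in the other. If they are counted, a significant chi-square test need not mean that screening found more true AF.

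The protocol has a safeguard in the two-cardiologist review, but leaves open whether it governs the endpoint. If it does not, strip errors count. If it does, only screening-arm cases face the stricter test. A reader of the trial report could not tell which standard produced either proportion.

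**Working it through.** **Inputs.** From the synopsis: "we assume to detect AF in 1% of patients in the control group and in 3% of patients in the intervention group". The sample size is put there at 745 per group for 80% power, raised to 800 per group to allow for losses. Two-sided alpha of 0.05 and 1:1 allocation are from sections 11 and 6.1. The primary test is the chi-square test (11.3.1).

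**The plan's own figure.** n = (1.960 + 0.842)² × (0.01×0.99 + 0.03×0.97) / 0.02² = 7.849 × 0.0390 / 0.0004 ≈ 766 per group (769 with pooled variance). At 745 per group the power is 78.8%; at 800 it is 81.6%. The stated 745 is close enough to accept.

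**How few cases decide the result.** The plan expects 0.01 × 800 = 8 control and 0.03 × 800 = 24 screening cases.
- 18 vs 8: pooled proportion 26/1600 = 0.01625; SE = √(0.01625 × 0.98375 × 2/800) = 0.00632; z = 0.0125/0.00632 = 1.977; chi-square 3.91, p ≈ 0.048.
- 17 vs 8: z = 0.01125/0.00620 = 1.81, not significant.

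Ten excess cases are enough.

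**Chance of a spurious positive trial.** Set true detection at 1% in both arms and let a net false-positive rate f apply to screening-arm patients without AF, so the observed screening rate is 0.01 + 0.99f. The documents give no value for f after physician reading, so 0 to 2% is an assumed range. Simulated Pearson chi-square tests, 400,000 trials per row, 800 per arm:

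| f | Observed screening rate | Expected false positives | Significant in favour of screening |
|---|---|---|---|
| 0 | 1.00% | 0 | 2.4% |
| 0.5% | 1.50% | 4.0 | 14% |
| 1% | 1.99% | 7.9 | 38% |
| 1.5% | 2.48% | 11.9 | 64% |
| 2% | 2.98% | 15.8 | 83% |

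A rate of f = 0.02/0.99 = 2.02% (about 16 patients) reproduces the planned 3% vs 1% with no true effect.

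**Per strip.** If strips err independently (an assumption), the per-strip rate giving f = 2.02% is 1 − (1 − 0.0202)^(1/k). That is 0.34% for k = 6, 0.20% for k = 10 and 0.10% for k = 20. Length of stay is not given, so this range of k is also assumed.

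**Upper bound.** Applying 92% specificity per patient with nothing corrected later gives 800 × 0.99 × 0.08 ≈ 63 false positives. The apparent rate is 0.01×0.96 + 0.99×0.08 = 8.9%.

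**If confirmation lowers the screening rate.** With control at 1% and 800 per arm, power is about 63% at a confirmed 2.5% and 38% at 2.0%. Restoring 80% would need 1199 or 2319 per group.

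**The case against.** The strongest reply is that the protocol is silent rather than wrong. Sections 3.6 and 12.3 put forward the cardiologist review as the answer to overdiagnosis and apply it to every device-found case. A natural reading is that a rejected case is not newly detected AF, so all that is missing is a cross-reference. External monitoring also includes a check of the main criterion. Part of this stands: the documents do not say that rejected cases count. Nor do they say that such cases are removed, and the section that defines the endpoint gives the decision to the investigators. The monitoring item does not say who confirms AF, or that both arms get the same review.

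More looking in one arm is the intervention itself, and the protocol explains why it uses no sham. That is accepted; the point concerns how findings are confirmed, not how often patients are recorded.

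Three stronger readings are tempting and not supported:

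- **Device-only cardiologist review itself creates the difference.** It can only remove screening-arm cases, so it would shrink the difference. Inflation comes from unconfirmed single-strip readings.
- **Control cases are never checked.** Section 9.3.3 offers the cardiology visit, with a 12-lead ECG, to all newly detected AF. What is missing is adjudication for the endpoint.
- **About 63 false positives should be expected.** Section 12.3 does not say whether 92% is per strip, per patient or after physician reading, and the synopsis sets the same figures beside a Holter comparison. An apparent rate of 8.9% also fits poorly with the community screening study cited in section 3.1, which found unknown AF in 3% over three weeks.

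**Conclusion.** The point holds in this form: the endpoint definition accepts a single unblinded reading, and the confirmation step planned elsewhere is not connected to it and does not reach the control arm. If the review does not decide the endpoint, the bias favours screening. Its size depends on a residual false-positive rate that the documents do not give, but a rate of about 1% already raises the chance of a spurious positive from 2.4% to 38%. If the review does decide the endpoint, the bias runs towards no difference. The conclusion that the arms are judged by different standards holds under both readings and does not depend on the 92% figure. This should be settled in the protocol before the primary outcome is compared, including at the planned interim analysis.

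**What to change.** State in section 9.2.1 that the primary outcome is newly detected AF on any ECG, in either arm, that meets the section's rhythm criterion and is confirmed by the two cardiologists already planned, with allocation masked as far as the tracing allows. Cases they reject do not count. Retrieve and archive control-arm tracings for the same review: sections 12.1 and 12.1.3 provide for storing Zenicor ECGs, but no storage is stated for routine tracings, and a lost control tracing would count against that arm. Report the investigators' unconfirmed count as a sensitivity analysis. Align sections 3.6 and 12.3 with this wording. This concerns counting for the endpoint only and changes no patient care.

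The direct cost is an amendment and review of about 8 control tracings (1% of 800) by reviewers already committed to the screening-arm cases. There are two downsides. Masking will be partial, because the strip format reveals the arm. And if confirmation brings the screening-arm rate below 3%, power falls as shown above, so the sponsor should restate the power for a confirmed endpoint.

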### **12.2.3 Electronic and central data validation**

The Zenicor ECG will be transmitted to a central server for clinical analysis of the data. The investigators will interpret the validity and diagnosis on the displayed results.

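### Section 9.2.1 does not tie the primary event to the promised two-cardiologist review, so residual false-positive strips can inflate the screening arm alone

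*Protocol*

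**What the plan says.** Section 9.2.1 names the endpoint ("The primary end point will be the proportion of newly detected atrial fibrillation"), the readers ("The one-lead ECGs will be reviewed by the investigating physicians through the Web-based analysis service") and the criterion: an irregular rhythm "in the absence of discernable p waves or the presence of f-waves in at least one of the ECG registration". Section 8.1.1 also gives the reading to the investigators, and so does section 12.2.3: "The investigators will interpret the validity and diagnosis on the displayed results". Section 6.2.2 states that nobody is blinded. Sections 5.1, 11.1 and 11.3.1 repeat the outcome, the null hypothesis and the comparison of proportions without adding a confirmation step.

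A second reading is promised elsewhere. Section 3.6, in answer to the risk of overdiagnosis, says "every case of new AF diagnosed by use of the screening method will be reviewed by two independent cardiologists". Section 12.3, in its risk assessment, says "each case of newly diagnosed atrial fibrillation by use of the Zenicor device will be examined by two independent cardiologists". Both add Holter or R-Test recordings when there is doubt. Section 12.3 also gives the device a "sensitivity of 96% and specificity of 92% in detection and diagnosis of atrial fibrillation when compared with 12-lead ECG" and says that its errors lean towards overdiagnosis.

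Under section 8.1.2, control patients have no systematic monitoring. Their AF is found by whatever routine care records.

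**The concern.** Section 9.2.1 is the only place that fixes when a patient counts as an event, and it does so without the review that 3.6 and 12.3 describe. Those two sections present the review as protection against wrong diagnosis and unneeded treatment. Neither says that it settles the primary outcome or what happens in the analysis when the cardiologists disagree with the investigator.

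Three features make this gap matter for the primary test:

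- Device strips exist only in the screening arm, so their false positives can be added to one arm only.
- Strips are taken at least twice daily and one positive is enough, so a small error per strip accumulates over the stay.
- The readers are investigators who know that every strip comes from the screening arm.

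If the endpoint is scored on the investigators' reading, reading error alone could contribute to rejecting the null hypothesis of section 11.1. The two-cardiologist review also covers only AF found with the device. AF found on routine ECG, in either arm, has no stated reader or confirmation.

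**Working it through.** **Inputs from the protocol.** Detection of 1% in control and 3% with screening, and 745 per group for 80% power with 800 enrolled (section 11.2); two-sided alpha of 0.05 (section 11); chi-square test (section 11.3.1); 1:1 allocation (section 6.1).

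**Reproducing the plan's figure.** With unpooled variance, n = (1.960 + 0.842)² × (0.01 × 0.99 + 0.03 × 0.97) / 0.02² = 7.849 × 0.0390 / 0.0004, which gives 766 per group against the stated 745. At 745 per group the power is 78.8% by the normal approximation and 81.2% by exact enumeration of the uncorrected chi-square. The sample size is sound, so the same set-up can carry the check.

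**How few false positives matter.** Take the 8 control cases expected at 1% of 800, and 18 screening cases. The pooled proportion is 26/1600 = 0.01625. The standard error is √(0.01625 × 0.98375 × 2/800) = 0.00632. Then z = (10/800)/0.00632 = 1.98, p = 0.048. Ten extra cases among 800 are enough. The whole planned 2-point difference equals a per-patient false-positive rate of 0.02/0.99 = 2.02%, about 16 patients.

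**Chance of a false win.** Let true detection be b in both arms, and let f be the per-patient false-positive rate that remains in the screening arm. The observed screening proportion is q = b + (1 − b)f. The chance that two-sided p < 0.05 in favour of screening is the sum of Bin(x; 800, b) × Bin(y; 800, q) over all pairs with z > 1.96. The values of f are assumptions.

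| f | Expected screening cases of 800 (b = 1%) | Chance, b = 1% | Chance, b = 3% |
|---|---|---|---|
| 0 | 8.0 | 2.4% | 2.5% |
| 0.25% | 10.0 | 6.7% | 4.7% |
| 0.5% | 12.0 | 14.2% | 7.9% |
| 1% | 15.9 | 37.9% | 18.2% |
| 2.02% | 24.0 | 83.9% | 51.8% |

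**From strips to patients.** With k independent strips and error s on each, f = 1 − (1 − s)^k. For an assumed k = 10, s = 0.05% gives f = 0.5%, and s = 0.1% gives f = 1.0%. The protocol does not state the number of strips per patient.

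**The stated specificity.** Taken once per patient and as the final error, 92% would mean f = 8%, so q = 0.01 + 0.99 × 0.08 = 8.9% (71 of 800) and a false win would be practically certain. If confirmation removed 90%, 95% or 99% of that 8% (also assumed), f would be 0.8%, 0.4% or 0.08% and the chance of a false win 27%, 11% or 3.4%.

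**The case against.** **Sections 3.6 and 12.3 already cover every device case.** A reader might infer from 9.2.1 that a strip rejected by both cardiologists still scores as AF. The text does not say so. Section 9.2.1 does not call the investigators' reading final, and a strip without the defining features does not meet its own criterion. Confirmed AF may well be what the sponsor intends. This stands, and it makes the problem a missing link, not a rule that counts known false positives. The link is still missing: nothing says how an overturned case is analysed.

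**The 92% figure is not a forecast.** A reader might compute 800 × 0.97 × 0.08 = 62 false positives beside 800 × 0.03 × 0.96 = 23 true ones. The documents do not support that as a prediction. They do not say whether 92% is per strip or per patient, or before or after a physician reads. The synopsis sets the same figures beside a Holter comparison, while 12.3 names 12-lead ECG. The screening study cited in section 3.1 found 3% new AF in total over three weeks of intermittent one-lead recording, so under its reading process (not described here) false positives could not have exceeded 3% of participants. This objection stands in full. The case here rests on 0.5% to 1%.

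**Other safeguards exist.** Poor recordings are repeated, and external monitoring verifies source data and evaluates the main criterion. These lower the error, but a monitor checks against the protocol's definition, which is the one in 9.2.1.

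**The unconfirmed control arm is not clearly a bias towards screening.** Control AF rests largely on 12-lead ECG, the reference named in 12.3. If the review did decide device cases, stricter confirmation in the screening arm would tend to be conservative. This stands: the argument for one standard is comparability, not a known direction of bias.

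**Adjudication detail belongs in an analysis plan or charter.** That is true of procedures for disagreement. It is less true of what counts as an event, which this protocol defines itself.

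**Conclusion.** The concern holds as a gap that should be fixed. The protocol defines its primary event on unblinded investigators' reading of any one strip and does not connect it to the confirmation it promises elsewhere.

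With 1% true detection in both arms and 800 per arm, 0.5% to 1% of screened patients wrongly classified would lift the chance of a false win from 2.4% to about 14% to 38%. If true detection is 3% in both arms, the rise is from 2.5% to about 8% to 18%. These figures assume the stated error rates, no added false positives in the control arm, and an endpoint scored without the cardiologists' decision. If their decision is already meant to count, the defect is one of wording, plus the absence of any stated confirmation for AF found on routine ECG.

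**What to change.** In section 9.2.1, and by reference in 11.3.1, state that:

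- the primary event is newly detected AF confirmed by the two-cardiologist review of sections 3.6 and 12.3 against the 9.2.1 criteria;
- cases they do not confirm count as no AF in the analysis;
- the proportion on the investigators' reading is reported as a sensitivity analysis;
- where the tracing is available, AF found on routine ECG in either arm goes through the same review against the same criteria.

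The text should not claim that this masks allocation. Removing labels cannot do so, because one-lead thumb strips arise only in the screening arm. The change concerns how events are classified for analysis and alters no patient's care.

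**Cost.** The cardiologists already see every device case. The extra work is retrieving and reading about 8 control tracings (1% of 800) and any routine-ECG cases in the screening arm. The screening-arm yield may come out lower than on the investigators' reading.

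Timing needs care. Version 4.0 is dated 13.08.2019. Planned first inclusion was 01.03.2018 with 15 months of enrolment, so on the planned dates recruitment would already have ended. Section 11.3.3 also foresees an interim comparison of the primary endpoint between the arms. The amendment should therefore record that the clarification was made without reference to results by arm or, if those were already known, say so.
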